#### 2.18.2. Software for Statistical Analyses

Statistical analysis will be performed using SPSS (version 26.0, SPSS Inc., Chicago, IL, USA) in the Clinical Evaluation Center of Shanghai General Hospital, which is affiliated to the Shanghai Jiaotong University.

### 2.19. Sample Distribution

The size and dropout rate of each data set will be described. Detailed reasons related to participants' withdrawal from the trial will be provided.

### 2.20. Baseline Information

Baseline-adjusted analyses will be conducted for center and severity variables, and the baseline value of the corresponding outcomes will be assessed. Descriptive statistics will be used to compare baseline measures with participant characteristics. If an imbalance occurs in the baseline characteristics between the two groups, the analysis of variance will be applied.

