## 2. Methods and Analysis

### 2.1. Design

A parallel-group, randomized, and single-blinded (outcome assessors) prospective clinical trial was designed according to the Consolidated Standards of Reporting Trials (CONSORT 2010) guidelines (Figure 1), Standards for Reporting Interventions in Controlled Trials of Acupuncture (STRICTA) [15, 16], and Standard Protocol Items—Recommendations for Interventional Trials (SPIRIT) statement (Figure 2) [17] and the SPIRIT checklist. Patients with ICUAW will be recruited from the Shanghai General Hospital, which is affiliated to the Shanghai Jiaotong University from October 2020 to September 2023. Participants will be screened based on the inclusion and exclusion criteria; briefed on the purpose, procedures, treatments, and possible risks of the trial; and informed of their rights to discontinue participation in the clinical study at any time point. Once participants will have signed the written consent forms, they will receive either 20 sessions of acupuncture plus rehabilitation training therapy or sham acupuncture plus rehabilitation training for 4 weeks. The study design flow chart and the schedule are presented in Figure 1 and Table 1, respectively. In this study, we will follow the methods of Shou et al. 2020 [18].

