### 2.21. Efficacy Analysis

Efficacy data analyses will be conducted based on the intention-to-treat population. All participants will be initially included in one of the two groups and considered in the statistical analyses. Analysis of efficacy will be conducted for each protocol and include all the participants who would complete the entire research processing. Descriptive statistics will be used to report primary outcome indicators between the two groups. All the data will be statistically analyzed using SPSS. All measurements will be expressed as mean ± standard deviation. The *t*-test will be used for comparisons between two samples if the distributions are normal, and the F-test will be used for comparisons among multiple samples. The Kruskal–Wallis H-rank sum test was used if the distribution is not normal. The participants' sex and course of disease will be recorded, and the data will be tested using the *χ*^2^ test. The ultrasound data will be analyzed by a mixed-effect model. The Cox-regression analysis will be performed to identify outcome-related factors. *P* < 0.05 will be considered as statistically significant.

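### Sections 2.20 and 2.21 give unreconciled analysis rules for the five ultrasound primary outcomes, and the imbalance-triggered analysis of variance would not correct an imbalance

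*Protocol article*

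**What the plan says.** Section 2.11 of the protocol article makes five ultrasound measures primary, compared between baseline and the end of the 4-week treatment. The analysis rules that reach them are these.

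- Section 2.20, without condition: "Baseline-adjusted analyses will be conducted for center and severity variables, and the baseline value of the corresponding outcomes will be assessed".
- Section 2.20, next to it and conditional: "If an imbalance occurs in the baseline characteristics between the two groups, the analysis of variance will be applied". It gives no threshold and no list of characteristics.
- Section 2.21: a t-test "will be used for comparisons between two samples if the distributions are normal"; otherwise the Kruskal–Wallis "H-rank sum test was used if the distribution is not normal". An F-test is added for more than two samples.
- Section 2.21, without condition: "The ultrasound data will be analyzed by a mixed-effect model".

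No sentence says which of these decides. The one sentence in section 2.21 that names the primary outcome indicators assigns them descriptive statistics only. On sites, section 2.1 says: "Patients with ICUAW will be recruited from the Shanghai General Hospital". Section 2.23 announces a separate statistical analysis plan.

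**The concern.** One ultrasound outcome can yield a p-value from a t-test, a rank test, an analysis of variance, a baseline-adjusted analysis and a mixed-effect model. Two of the switches between them, baseline imbalance and normality, are thrown by the data, and the first has no definition. Section 2.20 also contradicts itself, since it adjusts regardless of balance and then acts only on imbalance.

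Two things are at stake. If the ranking is settled only once results are visible, the nominal 5% level no longer describes the procedure. And if an unadjusted test ends up deciding, the baseline ultrasound value, which Table 1 schedules for everyone, goes unused.

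**Working it through.** **Inputs.** From the document: 28 per group (abstract) and significance level 0.05 (section 2.21, taken as two-sided). Assumed, because the document gives none: correlation ρ between baseline and week-4 values of 0.3, 0.5 or 0.7. The plan states no error rate or precision figure on this point, so there is none to reproduce.

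**1. Does the triggered analysis of variance correct an imbalance?** Take *n* per group, mean difference *d* and pooled variance *s*².
- t = d / (s√(2/n)), so t² = n·d² / (2s²).
- One-way ANOVA with two groups: F = between-group mean square / within-group mean square = (n·d²/2) / s² = n·d² / (2s²) = t².

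At n = 28 both equal 14·d²/s². The p-value is the same and baseline appears nowhere. Only a model with the baseline value as a covariate would adjust for it.

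**2. Can center be fitted?** With one hospital the center column is constant and collinear with the intercept, so no coefficient can be estimated.

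**3. What do the triggers do to type I error?** Simulated trials with no treatment effect, 28 per group, 6,000 per setting, normal and lognormal data, ρ = 0.3, 0.5, 0.7. The Monte Carlo standard error at 5% is √(0.05 × 0.95 / 6000) = 0.28 percentage points. The triggered branch was given the generous reading, ANCOVA. Normality was judged by the Shapiro–Wilk test.

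| Procedure | Share with p < 0.05 over the six settings |
|---|---|
| ANCOVA, fixed in advance | 4.9% to 5.7% |
| Change-score t-test or Kruskal–Wallis by normality | 5.2% to 5.7% |
| ANCOVA only if baseline is imbalanced (p < 0.05, or standardised difference > 0.25), else change-score t-test | 3.2% to 4.7% |
| Both triggers (imbalance at p < 0.05) | 4.3% to 5.0% |
| Smallest p of t-test, Kruskal–Wallis, ANCOVA | 7.6% to 9.4% |
| The same with a week-4 t-test added | 10.3% to 11.5% |

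A separate simulation of 8,000 null trials per setting put the smallest of three p-values below 0.05 in 8.3%, 7.7% and 7.4% of trials at ρ = 0.3, 0.5 and 0.7. If the triggered branch is instead a plain ANOVA, step 1 shows that it returns the t-test's own p-value, so that trigger changes nothing.

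**4. What would an unadjusted test cost?** With equal variance σ² at both visits, the variances per patient are 2σ²(1 − ρ) for the change score, σ² for the week-4 value alone, and σ²(1 − ρ²) for ANCOVA.
- Change score / ANCOVA = 2(1 − ρ)/(1 − ρ²) = 2/(1 + ρ): 2/1.3 = 1.54, 2/1.5 = 1.33, 2/1.7 = 1.18.
- Week-4 value / ANCOVA = 1/(1 − ρ²): 1/0.91 = 1.10, 1/0.75 = 1.33, 1/0.51 = 1.96.

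For illustration, with 23 per group, a true effect of 0.6 SD and ρ = 0.5 (the last two assumed), simulated power is 62% with ANCOVA, 51% with the change-score t-test, and 51% to 55% with adjustment only on imbalance.

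**The case against.** The strongest reply is that section 2.21 does assign a method. All five primary outcomes are ultrasound measures, the mixed-effect model is given to ultrasound data without condition, and the t-test and rank-test sentences can be read as generic rules for other measures such as the MBI and MRC scores. This is a reasonable reading, and the fix builds on it. But the text does not call the model primary, does not exempt ultrasound data from the generic rules, and does not say how the model relates to section 2.20.

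A second reply is that a condensed article may leave model terms and contrasts to the announced statistical analysis plan. That is right for detail that is merely absent, and nothing here rests on such detail. It does not cover rules that are stated and conflict: a plan that fixes one method will have to depart from part of this text.

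A third is that analysis of variance may stand for analysis of covariance. The remedy would then work, but it would still hang on an undefined trigger beside an unconditional statement.

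A reader might infer that the imbalance and normality triggers themselves inflate the error rate. The simulation does not support that. The 7% to 9% belongs to an analyst who runs all three tests and keeps the smallest p-value, which the protocol nowhere sanctions. The mixed-effect model itself was not simulated; week-4 ANCOVA stood in for the adjusted analysis.

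**Conclusion.** The point holds as an unresolved conflict between stated rules, with two plain errors inside it: a remedy for imbalance that does not adjust for baseline, and a center covariate in a one-hospital trial. The center error is one of wording, because a constant term simply drops out.

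Applied mechanically, the triggers keep type I error at about 3% to 6%. The exposure, about 7% to 9% for the best of three tests, arises only if the choice is made after the data are seen. It rests on the simulated distributions and on ρ between 0.3 and 0.7.

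A reader might also infer that the trial is bound to lose precision. The document does not establish this: section 2.20 points towards adjustment, and no sentence makes an unadjusted test decisive. The ratios 1.54, 1.33 and 1.18 apply only if a change-score t-test decides, and at correlations that the document does not supply. The text should be corrected, but it does not show that the trial's result will be wrong.

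**What to change.** In sections 2.20 and 2.21:

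1. State that the mixed-effect model already named is the primary analysis of each ultrasound outcome, and that its week-4 treatment contrast decides.
2. Always include the baseline value of that outcome and one pre-specified severity variable, for example the APACHE II score, whatever balance is observed.
3. Delete the imbalance-triggered analysis of variance and the center covariate.
4. Make the t-test and rank test sensitivity analyses for the ultrasound outcomes, so that normality no longer selects the deciding test.

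The cost is wording in the protocol or the statistical analysis plan, before the data are seen. The baseline ultrasound values (Table 1) and APACHE II (section 2.10.1) are already collected. The change settles which test decides within each outcome. How five primary outcomes share the 5% level is a separate question that it does not answer.

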### 2.21. Efficacy Analysis

Efficacy data analyses will be conducted based on the intention-to-treat population. All participants will be initially included in one of the two groups and considered in the statistical analyses. Analysis of efficacy will be conducted for each protocol and include all the participants who would complete the entire research processing. Descriptive statistics will be used to report primary outcome indicators between the two groups. All the data will be statistically analyzed using SPSS. All measurements will be expressed as mean ± standard deviation. The *t*-test will be used for comparisons between two samples if the distributions are normal, and the F-test will be used for comparisons among multiple samples. The Kruskal–Wallis H-rank sum test was used if the distribution is not normal. The participants' sex and course of disease will be recorded, and the data will be tested using the *χ*^2^ test. The ultrasound data will be analyzed by a mixed-effect model. The Cox-regression analysis will be performed to identify outcome-related factors. *P* < 0.05 will be considered as statistically significant.

### 2.22. Safety Analysis

According to the definition of AEs, AEs will be recorded in conjunction with their severity level, causes, and explanations. Moreover, the number and the rate of AE will be described statistically. If AEs would be required to be compared between groups, the *χ*^2^ test or the Fisher's exact test will be used for statistical analyses.

### 2.23. Missing Data Analysis

All data used in the main statistical analyses will be collected by the fourth week of the treatment and end of the 3-month follow-up period. If any of the data are not obtained, the assumed missing data mechanism will be analyzed, and a multiple adjustment approach will be used. After the main analysis, a sensitivity analysis will be performed for the various data sets to enable an assessment of the impact of the missing data on the results. A fully specified statistical analysis plan will be written independently.

### 2.24. Publication and Dissemination

Following the completion of data analyses, Chinese and English language disseminations will be planned. Trial results will be disseminated via conferences or publications. No public access will be provided to the entire protocol, participant data sets, or statistical code. However, scientists will be able to gain access to the full protocol through the Ethics Committee of the Institute of Shanghai General Hospital upon request. This protocol was written following the SPIRIT checklist. The future report will follow the CONSORT guidelines [13], revised STRICTA [12], and the extension of CONSORT for reporting single-blinded randomized trials.

## 3. Discussion

ICUAW is a frequent complication of critical illness, with devastating short- and long-term consequences. Therefore, effective prevention and/or treatment of ICUAW are required. Currently, the prevention of ICUAW development seems, at least in part, possible. However, to date, there is no effective therapeutic strategy to treat the disease [27, 28]. Some studies have shown that early rehabilitation has a positive effect on ICUAW recovery, shortens ICU and hospital stays, decreases the duration of mechanical ventilation, improves long-term functional independence, and reduces mortality [29–31]. However, a systematic review could not support the fact that post-ICU physical rehabilitation was beneficial because of the lack of high-quality data and existence of heterogeneity [32]. Another randomized controlled trial including 120 patients with acute respiratory failure found that the length of ICU and hospital stays were longer in the intervention group compared with those in the control group [33]. The early rehabilitation during ICU stay was not associated with improvements in functional status, muscle strength, quality of life, or healthcare utilization outcomes, although it seemed to improve walking ability compared with usual standard care [34, 35]. Thus, additional studies are required to design new preventive and/or therapeutic strategies that can be tested in adequately powered, large-scaled, well-performed, randomized controlled trials. Therefore, we developed the protocol of a randomized controlled trial presented herein to assess the effectiveness and safety of acupuncture combined with rehabilitation training for the treatment of patients with ICUAW.

Acupuncture is a feasible, safe, and acceptable therapy in ICU settings for patients with diversity backgrounds [36]. The therapeutic advantage of using acupuncture as an adjuvant therapy lies in the fact that the combination benefits the respiration of ICU patients on ventilation machine and helps weaning from prolonged ventilation [37]. The application of transcutaneous electrical nerve stimulation on acupuncture points has been shown to decrease the level of pain and opioid consumption in intubated patients connected to mechanical ventilators [38]. In addition, combined therapy of acupuncture with herbal medicine has been found to reduce the incidence of delirium in patients with cardiovascular disease in ICUs [39]. Furthermore, it is known that acupuncture with oral administration of essential amino acids is more effective and the combination can increase muscle mass in a relatively shorter time than treatment with the essential amino acids alone [11]. Recent studies have demonstrated that acupuncture can counteract skeletal muscle atrophy by increasing IGF-1 levels and by stimulating muscle regeneration [40]. In this report, we designed a single-blinded, randomized, sham-procedure-controlled, clinical trial with a 3-month follow-up for the assessment of the efficacy of acupuncture combined with rehabilitation training in patients with ICUAW. Successful completion of the proposed clinical trial will provide strong evidence that the therapeutic regimen of acupuncture combined with rehabilitation training is more effective than the rehabilitation training alone for the treatment of the ICUAW. The findings of this study could help to develop a better strategy for the treatment of the ICUAW disease and expand the application of acupuncture technique in clinical settings.

In this study, we proposed the use of muscular ultrasonography to evaluate the muscle strength by visualizing the muscle's cross-sectional area, layer thickness, and echo intensity based on the grayscale and penetration angle [41]. This is because the ultrasonic measurement of muscle thickness can be used to assess the presence of sarcopenia, and the echo intensity can be associated with muscle strength and correlated with the risk of frailty in elderly outpatients [25, 26]. We believe that muscle ultrasound can reliably detect the pathological changes of ICUAW [41]. Our study will address whether this treatment will affect the quadriceps femoris muscle area, thickness, vastus intermediate muscle thickness, subcutaneous tissue thickness, ultrasonic intensity of the rectus femoris, and MBI and MRC total scores in the long term after the last treatment.

## Figures and Tables

**Figure 1 fig1:**
[figure not shown]
Flow chart of the study design.

**Figure 2 fig2:**
[figure not shown]
Total study period and evaluation time points.

**Table 1 tab1:** Study design schedule.

Period	Baseline	Treatment (W1–W4)		Follow-up (W12)
Time	W0	W2	W4	W12
Eligibility	X			
Demography and medical history	X			
Physical examination	X			
Informed consent	X			
Quadriceps femoris muscle area	X	X	X	X
Quadriceps femoris muscle thickness	X	X	X	X
Vastus intermediate muscle thickness	X	X	X	X
Subcutaneous tissue thickness	X	X	X	X
Ultrasonic intensity of the rectus femoris	X	X	X	X
MBI	X	X	X	X
MRC	X	X	X	X
Adverse event			X	X
Compliance		X	X	

“X” indicates Yes. MBI: Modified Barthel Index; MRC: Medical Research Council.

**Table 2 tab2:** Acupoints and needle procedure.

Acupoints	Angle and direction	Depth (mm)
Jianyu (LI15)	Straightly	8
Quchi (LI11)	Straightly	8
Zusanli (ST36)	Straightly	13
Yanglingquan (GB34)	Straightly	13
Biguan (ST31)	Straightly	13

## Data Availability

The data used to support the findings of this study will be available from the corresponding author upon request.
